### Block effect evaluation

Complete block: There is no significant fluctuation of the HR, BP, and RR during the operation (heart rate and blood pressure increased by less than 10% compared with the baseline value, and respiratory rate increased by less than 20%). Partial block: When a non-single nerve innervates the surgical site, there is a specific innervated area that causes HR, BP, and RR fluctuations (HR, BP increase ≥ 10% from the baseline value, RR increase ≥ 20%), while there is no significant fluctuation in operation in other innervated area. Block failure: Operation in any innervated area caused substantial changes in HR, BP, and RR. For partial block and failure of block, a single dose of sufentanil (0.01 μg/kg) and a pump of 0.1–0.2 μg/kg/min remifentanil for supplementary analgesia.

### Data collection and management

Record the PI values of the index finger and little finger on blocked and non-blocked sides in all children. Data collection and completion will be carried out by two research assistants blinded to the grouping of subjects. The clinical trial supervisors will periodically review the quality of data entry to ensure the authenticity and reliability of the program. This data supervision committee has no conflict of interest in the study. All information related to the study will be stored securely.

### Statistical analyses

Analyses will be performed using SPSS statistical software (version 19.0). Categorical variables are represented by frequency, and continuous variables are represented by mean ± standard deviation or median [interquartile range]. Chi-square test or Fisher test will be used for comparison between groups of classified variables, and *t*-test, analysis of variance, or rank-sum test will be used for comparison between groups of continuous variables. A logistic regression model will be used to analyze the influencing factors of anesthesia effect and complications, and stepwise regression will be used to screen independent variables. If data were missing, patients would be excluded from the specific analysis.

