### Interventions

The children will be given a slow intravenous bolus of 0.1 mg/kg midazolam for sedation during the waiting period. After entering the operating room, routinely monitor the electrocardiogram (ECG), heart rate (HR), blood pressure (BP), respiration rate (RR), and pulse oxygen saturation (S_P_O_2_). SEV group: Inhalation of sevoflurane (5%-8%) for induction of anesthesia, sufentanil 0.2 μg/kg, penehyclidine hydrochloride 0.01mg/kg, dexamethasone 0.1 mg/kg. Place the laryngeal mask, and maintain anesthesia with 1.0 MAC value of sevoflurane + 50% oxygen. PRO group: propofol 3 mg/kg, sufentanil 0.2 μg/kg, penehyclidine hydrochloride 0.01 mg/kg, dexamethasone 0.1 mg/kg are given for anesthesia induction. Place the laryngeal mask, and propofol 3 mg/kg/h is given for anesthesia maintenance. Then, all children will be placed supine with their heads tilted to the opposite side. Under ultrasound guidance, an experienced anesthesiologist will use an in-plane needle to block the supraclavicular nerve and give 0.25% ropivacaine 0.4 ml/kg.

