### Outcomes

#### Primary outcome

The primary outcome is to assess the effects of PI on the success of supraclavicular brachial plexus block in pediatric patients under sevoflurane or propofol general anesthesia. PI values of the index finger and little finger will be recorded before induction of general anesthesia in the operating room, immediately after laryngeal mask placement, 5 min, 10 min, 15 min after SCB, immediately after surgery, after removal of laryngeal mask when the child is awake and in PACU. Record the dosages of opioids and vasoactive drugs during the operation. Evaluate the complications and recovery quality in children. (1) Assessment of restlessness and delirium during the recovery period and 30 min in PACU. (2) Postoperative pain score. Postoperative complications: nausea and vomiting, neurological dysfunction, Horner syndrome, respiratory depression, etc.

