#### Secondary outcomes

The secondary outcome includes mean arterial blood pressure (MAP), heart rate (HR), and PI ratio (correlation between baseline PI and 10min after SCB). The age, gender, ASA classification, BMI, anesthesia time, operation time, anesthesia recovery time, duration of stay in PACU, and duration of postoperative hospital stay will be recorded.

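### The sevoflurane–propofol comparison of mean PI, MAP and HR is planned without covariates, although pre-induction PI and age are recorded: a loss of precision, not of validity

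*Protocol article*

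**What the plan says.** The Statistical analyses section of the protocol article names the methods for continuous variables: the t-test, "analysis of variance, or rank-sum test will be used for comparison between groups of continuous variables". It names no covariate. The one multivariable method has a different target: "A logistic regression model will be used to analyze the influencing factors of anesthesia effect and complications", with stepwise selection. It does not take PI, MAP or HR as the outcome.

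The candidate covariates appear elsewhere in the article:

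- **PI.** Under Primary outcome: "PI values of the index finger and little finger will be recorded before induction of general anesthesia in the operating room", followed by readings through surgery and recovery.
- **HR and BP.** Under Interventions, on entry to the operating room and ahead of the induction steps, staff are to "routinely monitor the electrocardiogram (ECG), heart rate (HR), blood pressure (BP", among other signs. Block effect evaluation relies on a baseline for both ("heart rate and blood pressure increased by less than 10% compared with the baseline value") but does not say when it is taken.
- **Age.** Under Secondary outcomes: "The age, gender, ASA classification, BMI, anesthesia time" and further items are to be recorded. Eligibility runs from 1 month to 12 years.

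MAP and HR are themselves outcomes: "The secondary outcome includes mean arterial blood pressure (MAP), heart rate (HR), and PI ratio".

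**The concern.** The trial is described as a randomised superiority trial with 1:1 allocation, and the Randomization section mentions no stratification by age. Pooling infants with 12-year-olds can be expected to give HR and MAP a spread between children that is unrelated to the anaesthetic. PI may likewise carry part of each child's own resting level. A t-test, ANOVA or rank-sum test leaves all of this in the error term, whereas a model with baseline and age removes whatever share they explain.

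What is at stake is the width of the intervals, and the power, for the between-arm differences in mean PI, MAP and HR. The article states no power for these differences. Using data already collected is the one way to sharpen them without enrolling more children.

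**Working it through.** **1. The plan's own figure.** Table 1 gives 37 + 10 = 47 per group at alpha 0.05 and beta 0.10. The article does not name the method. The larger number in all 16 cells is reproduced by the sample size for an area under the ROC curve A of 0.80 against 0.50, with a 4:1 ratio, two-sided alpha and the large-sample Hanley–McNeil variance. The 0.80 is inferred from this match; it is not stated.

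- Variance term: V(A) = (Q₁ − A²)/0.25 + (Q₂ − A²), with Q₁ = A/(2 − A) and Q₂ = 2A²/(1 + A).
- V(0.5) = 0.0833/0.25 + 0.0833 = 0.4167, root 0.6455.
- V(0.8) = 0.0267/0.25 + 0.0711 = 0.1778, root 0.4216.
- n = [(1.960 × 0.6455 + 1.282 × 0.4216)/0.30]² = 36.2, rounded up to 37. The smaller group is 37/4 = 9.25, rounded up to 10.
- Withdrawal: 47 × 1.1 = 51.7, rounded up to 52 per group and 104 in total.

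So the sample size fits a discrimination analysis within each group. The comparison of mean PI, MAP or HR between arms was not what set it.

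**2. Inputs for the between-arm comparison.** n = 47 per arm (the number before the withdrawal allowance) and two-sided alpha 0.05. The article gives no SD, no target difference and no correlation. The difference is therefore expressed in SD units, and rho, the joint correlation of the covariates with the outcome, is an assumption varied from 0.2 to 0.7.

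**3. Unadjusted test.** Noncentral t with 92 degrees of freedom and noncentrality d × √(n/2). Power of 80% corresponds to d = 0.584, since 0.584 × √23.5 = 2.83. Power of 70% corresponds to d = 0.518.

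**4. Adjusted model.** The error variance becomes (1 − rho²) times the unadjusted one, so the effective difference is d/√(1 − rho²), with one degree of freedom fewer. Example at rho 0.5: 0.584/√0.75 = 0.674.

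| rho | Error variance | Interval narrower by | Power (80% unadjusted) | Equivalent n per arm, 47/(1 − rho²) |
|---|---|---|---|---|
| 0.2 | ×0.96 | 2.0% | 81.6% | 49.0 |
| 0.3 | ×0.91 | 4.6% | 83.6% | 51.6 |
| 0.4 | ×0.84 | 8.3% | 86.4% | 56.0 |
| 0.5 | ×0.75 | 13.4% | 89.9% | 62.7 |
| 0.6 | ×0.64 | 20.0% | 93.8% | 73.4 |
| 0.7 | ×0.51 | 28.6% | 97.5% | 92.2 |

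From 70% unadjusted power (d = 0.518), power at rho 0.5 is 81.8%. A second covariate costs one more degree of freedom and changes these figures by at most 0.1 percentage point. With 52 per arm the relative gains are the same.

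**5. A change score is not a safe substitute.** Its variance is 2(1 − rho) times the unadjusted one, where rho is now the correlation with baseline alone. From 80% unadjusted, power is 65.8% at rho 0.3, 80.0% at 0.5 and 95.1% at 0.7. It is worse than no adjustment below 0.5.

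**The case against.** **The main question lies elsewhere.** A reader might infer that the trial's central conclusion is weakened. The article does not support that. Its Design section asks under which anaesthetic PI better judges the block, which compares discrimination and not mean PI, and the sample size fits the same purpose. Adjusting mean PI, MAP or HR would not sharpen that answer. This stands and limits the point to the between-arm means.

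**Chance imbalance.** A reader might also infer that an imbalance in age or resting values would bias the comparison. It would not: under randomisation the unadjusted test is unbiased, and its error rate already allows for such imbalance. Only precision is at issue.

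**The gain is assumed.** This stands. The 80% starting point is a reference, not a planned power, and at rho 0.3 the gain is under 4 percentage points. For PI the Discussion gives a reason to expect little: both anaesthetics dilate vessels, and PI may reach a ceiling that the block cannot raise further. That would loosen the link with an awake reading.

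**The HR and MAP baseline is not established.** This stands in part. Monitoring before induction is stated, but no recording time is given, and the baseline in the block definition could be a later reading. Only pre-induction PI and age are clearly recorded.

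**Missing data.** The plan excludes children with missing data from the analysis concerned. Under that rule, an adjusted model would drop a child without a pre-induction reading whom the unadjusted test keeps. This stands, and the fix has to deal with it.

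**Condensed article.** Covariates are often left to a fuller document. Here, however, the article itself names the tests, so this is a comment on a stated method and not on a gap. A fuller plan might add adjustment; the article gives no sign of it.

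**The PI ratio already uses baseline.** It does so for one measure at one time (10 min). That is not covariate adjustment, and it leaves MAP, HR and the other PI readings as they are.

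**Conclusion.** The point holds as one of efficiency. The stated tests are valid, but they ignore age and pre-induction PI, which are recorded, and pre-induction HR and BP, whose recording is implied but not given a time. Starting from 80% unadjusted power with 47 per arm, adjustment would give about 84% at a correlation of 0.3, 90% at 0.5 and 97.5% at 0.7. The gain is small at 0.3 or below and material at 0.5 or above. The article does not show where in this range the trial lies. It may be low for PI; for HR and MAP the wide age range makes a useful gain more plausible. The change is worth making because it costs so little, not because any conclusion is invalid without it.

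**What to change.** In Statistical analyses, make the between-arm analysis of PI, MAP and HR a linear model: ANCOVA at a given time, or a mixed model over the scheduled times. Include:

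- randomised arm;
- age as a continuous covariate;
- the child's pre-induction value of the same measure (same finger and side for PI), with PI on the log scale if skewed.

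State that the HR and MAP baseline in this model is the pre-induction reading. The reading after laryngeal mask placement should not serve as the covariate, because the assigned anaesthetic has already acted on it. Keep the unadjusted test as a sensitivity analysis.

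Add an exception to the missing-data rule: a child who lacks only the baseline reading stays in, with a simple imputed baseline derived from both arms together without using arm or outcome.

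The cost is a few sentences, one or two degrees of freedom, and a fixed recording time for HR and MAP before induction. The PI readings and age are already to be collected, and SPSS fits the model.

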Currently, studies found that PI can be used to evaluate the effect of nerve block primarily focused on awake adults [16, 17]. Xu Z reported that PI provides an earlier and more sensitive indicator to assess the onset of caudal block under ketamine anesthesia [18]. Still, there is a lack of relevant research on the effect of peripheral nerve block in children. The supraclavicular brachial plexus block (SCB) can be used for surgical anesthesia and analgesia of the upper arm, elbow, forearm, wrist, and hand below the shoulder joint. Therefore, the aim of this study is to evaluate the effect of PI on predicting the success of SCB in children under general anesthesia with sevoflurane and propofol.

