## Methods and design

### Aim of the study

This study aims to describe the role of PI in evaluating the predictive effect of SCB in children under general anesthesia with sevoflurane and propofol. Meanwhile, whether PI could predict the success of SCB by reflecting the impact of ulnar nerve block.

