### Design of the study

This is a parallel, 2-arm randomized superiority trial (protocol version 1.0, 05.22.2020). Tongji Hospital affiliated to Tongji Medical College of Huazhong University of Science & Technology acting as the sponsor. Pediatric upper limb surgery cases will be collected in Tongji Hospital from May 2020 to December 2022. Children were divided into propofol and sevoflurane groups by the random number table method. PI values of the index finger and little finger in the blocked and non-blocked sides will be recorded in all children. Analyzing the possible relationship of the changes in PI values with complete block, partial block, and block failure in each group. A comparative analysis of sevoflurane and propofol block cases will determine whether PI can better judge the effect of supraclavicular brachial plexus block in which general anesthesia in children. The flowchart of this study is presented in Fig. 1. The schedule of enrollment, interventions, and assessments is shown in Fig. 2.

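### The primary question is how well PI predicts block success, but the stated methods include no diagnostic-accuracy analysis

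*Protocol article*

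**What the plan says.** The question is put as one of prediction throughout. The Introduction intends to "evaluate the effect of PI on predicting the success of SCB in children under general anesthesia with sevoflurane and propofol". The Aim of the study says "This study aims to describe the role of PI in evaluating the predictive effect of SCB in children under general anesthesia". Under Primary outcome: "The primary outcome is to assess the effects of PI on the success of supraclavicular brachial plexus block in pediatric patients".

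Design of the study sets two analysis tasks. The first is "Analyzing the possible relationship of the changes in PI values with complete block, partial block, and block failure in each group". The second is a comparison of the arms to determine "whether PI can better judge the effect of supraclavicular brachial plexus block in which general anesthesia in children".

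The Statistical analyses section then names its methods:
- chi-square or Fisher tests for categorical variables;
- for measured quantities such as PI, "analysis of variance, or rank-sum test will be used for comparison between groups of continuous variables", with Student's test as the remaining option;
- for block effect and adverse outcomes, a regression with stepwise selection of variables, in these words: "A logistic regression model will be used to analyze the influencing factors of anesthesia effect and complications".

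On the data themselves, Data collection and management says: "Record the PI values of the index finger and little finger on blocked and non-blocked sides in all children". The Primary outcome section lists seven or eight recording times, depending on whether awake and PACU count as one.

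**The concern.** A difference in mean PI between block categories, or a significant regression coefficient, shows that PI and block success are associated. It does not say how often PI classifies a child correctly, which is what a predictor of block success has to show. None of the named methods gives that figure.

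The same gap affects the comparison of anesthetics. Whether PI judges the block better under one drug is a question about two accuracies. Comparing PI levels between arms answers a different question, and the Discussion itself says that both drugs alter PI.

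At stake is whether the trial reports a result for its primary question. If the accuracy measure, finger, side and time are chosen after the data are seen, from about 28 to 32 readings per child (2 fingers × 2 sides × 7 or 8 times), the choice is also open to selection.

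**Working it through.** **1. Question against method**

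| What the article asks | Where | Named method that delivers it |
|---|---|---|
| Does PI predict block success? | Introduction; Aim; Primary outcome | None for accuracy. Logistic regression gives association, if PI is entered |
| How do PI changes relate to complete, partial and failed block, per arm? | Design of the study | Between-group tests compare PI levels across categories |
| Under which anesthetic does PI judge the block better? | Design of the study | None |
| PI across sides, fingers and times in one child | Primary outcome; Data collection and management | No paired or repeated-measures method named |

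The study that the Discussion builds on is reported there as cut-offs (PI ratio 1.4, increment 3.3 at 10 min) with sensitivity and specificity.

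**2. What Table 1 appears to size**

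From the Sample size section: insufficiency below 20%, alpha 0.05, beta 0.10, chosen cell 37 + 10 = 47. Assumed, because the article gives no effect size: AUC 0.80 against 0.50, 4:1 split, two-sided test, Hanley-McNeil variance with m in the positive class and n in the other:

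Var(A) = [A(1−A) + (m−1)(A/(2−A) − A²) + (n−1)(2A²/(1+A) − A²)] / (mn)

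Solve 1.960·SE(0.50) + 1.282·SE(0.80) = 0.30 with m = 4n, taking successes as the positive class. The solution is m = 37.17, n = 9.29, with SE(0.50) = 0.1070 and SE(0.80) = 0.0704. Check: 0.2097 + 0.0903 = 0.3000.

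Rounding m down to 37 and a quarter of it (9.25) up to 10 gives the printed 37 + 10. The same rule reproduces all 16 cells exactly. Rounding both classes up gives 38 + 10 = 48. AUC 0.90 against 0.60 with the classes swapped agrees with 15 of the 16 cell totals to within a small rounding tolerance, so the AUC form is better supported than the particular AUC values. The step to 52 per group is 47 × 1.1 = 51.7.

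**3. What an accuracy analysis would deliver at this size**

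The formula depends on which class is called positive, so both are shown. At 37 + 10 and AUC 0.80:
- successes positive: (0.16 + 36×0.02667 + 9×0.07111)/370 = 0.00476, SE 0.069, half-width 1.96×SE = 0.135;
- failures positive: (0.16 + 9×0.02667 + 36×0.07111)/370 = 0.00800, SE 0.089, half-width 0.175.

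With 38 + 9 these become 0.139 and 0.184.

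Power to show a between-arm AUC difference, 37 + 10 in each arm, is Φ(Δ/√(SE₁² + SE₂²) − 1.96):

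| AUCs | Failures positive | Successes positive |
|---|---|---|
| 0.80 v 0.90 | 14% | 23% |
| 0.75 v 0.90 | 25% | 38% |
| 0.70 v 0.90 | 38% | 54% |

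With 10 failures in an arm, 9 of 10 classified correctly has an exact 95% CI of 0.55 to 1.00.

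**The case against.** The best defense is that an article condenses a fuller plan, and that the logistic regression of anesthesia effect could carry the primary question. Part of this stands. A reader might infer that the plan uses only independent-sample tests and cannot address the question at all. The text does not support that: with PI in the logistic model, association with block success would be tested. But PI is not named as a predictor, stepwise selection could drop it, and no accuracy measure is drawn from the model. At 20% failures there are about 10 per arm and 0.20 × 104 ≈ 21 overall, which supports very few variables. Nor is this only detail left for later: the section lists its methods, and the list does not match the aim.

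A reader might also infer that paired readings will be mishandled. The article does not say so. The named tests are for comparisons between groups, a word that it uses for the two arms, where independent-sample tests at one time point are proper. Analysis of variance could also include a repeated-measures form. All that can be said is that no within-child method is named. A figure for power lost by unpaired testing of the two sides would measure a test that the plan never assigns. Bias from a cut-off picked on the data would likewise belong to a search that the plan does not state.

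Finally, the article nowhere calls Table 1 an AUC calculation. That remains an inference, though agreement in all 16 cells makes it a strong one.

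**Conclusion.** The concern holds as a mismatch between the primary aim and the stated analysis. The methods section contains no diagnostic-accuracy analysis of PI for block success, and none that compares accuracy between anesthetics. This conclusion rests on the text alone. The further point, that the trial seems to have been sized for a test that its analysis section omits, rests on the assumed AUC 0.80 against 0.50, 4:1 split and two-sided alpha.

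Adding the analysis will not make the trial precise. The AUC half-width is about 0.14 to 0.18 per arm at an AUC of 0.80. Power for a between-arm difference of 0.10 to 0.20 is about 14% to 38% with failures as the positive class, or 23% to 54% with successes. These figures assume about 10 failures per arm; the article's own rate is below 20%, and fewer failures would widen the intervals.

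**What to change.** Amend the Statistical analyses section before the data are analyzed:

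1. **Primary analysis.** Within each arm, the ROC AUC with 95% CI of one pre-named PI measure for complete against not-complete block. A natural candidate is the blocked-side PI ratio at 10 min, already listed under Secondary outcomes. State the finger, the baseline reading, and that it is a ratio, since that section describes it as a correlation.
2. **Between arms.** The AUC difference with its CI, reported as an estimate only and not as a powered test.
3. **Classification.** Sensitivity and specificity with exact CIs. Use the adult ratio of 1.4 from the Discussion as a secondary external benchmark only, because it comes from adults and the Discussion says both anesthetics change PI. Correct any cut-off derived from the trial's own data for optimism, for example by bootstrap.
4. **Repeated readings.** For comparisons across sides, fingers and times, name a mixed model with child as random effect, or a repeated-measures analysis of variance.
5. **Sample size.** State the basis of Table 1, including the AUC values if it is an AUC calculation.

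The cost is protocol wording and a little more analysis work. All the data are already being collected. The price in reporting is wide intervals, which should be acknowledged in advance.

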### Sample size

According to literature reports [15], the probability of ulnar nerve insufficiency is less than 20%; the sample size is calculated: As shown in Table 1, the preliminary estimated sample size is 47 cases, and the withdrawal rate is assumed to be 10%. The calculation is 52 cases per group, so 104 children will be included in this experiment.

**Table 1 Tab1:** Sample size estimation results

		Type I Error- Alpha			
		0.20	0.10	0.05	0.01
Type II Error -Beta	0.20	16 + 4	23 + 6	30 + 8	46 + 12
	0.10	21 + 6	29 + 8	**37 + 10**	54 + 14
	0.05	26 + 7	35 + 9	43 + 11	62 + 16
	0.01	37 + 10	47 + 12	57 + 15	78 + 20

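### Stepwise screening for the block-effect model will often admit noise variables, and nothing in the text keeps PI, the anaesthetic group or their interaction in the model

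*Protocol article*

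**What the plan says.** The Statistical analyses section of the protocol article states: "A logistic regression model will be used to analyze the influencing factors of anesthesia effect and complications". It then adds that "stepwise regression will be used to screen independent variables". The other methods there are descriptive summaries and between-group tests, so this regression is the only stated method that relates several predictors to block effect. The section gives no list of candidates and no entry or removal threshold. It does not say that any term stays in regardless of its p-value.

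The variables available are those recorded under Secondary outcomes: "The age, gender, ASA classification, BMI, anesthesia time, operation time, anesthesia recovery time, duration of stay in PACU" and postoperative hospital stay, besides MAP, HR and PI ratio. PI at two fingers and the randomised group come on top.

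On size, the Sample size section assumes that "the probability of ulnar nerve insufficiency is less than 20" per cent, arrives at 47 per group and 52 after withdrawals, and concludes "so 104 children will be included in this experiment".

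Design of the study sets the question: under which of the two anaesthetics does PI judge the block better?

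**The concern.** Stepwise selection tests each candidate and keeps what passes. With several candidates, something passes by chance in a large share of trials. The selected variables then carry odds ratios and p-values computed as if no search had taken place, so both are biased away from the null. In a trial about prediction, the apparent discrimination of such a model is also too good.

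The second problem is what the model may lack. The question in Design of the study needs PI, anaesthetic group and their interaction. Under a screening rule with no retained terms, each of these appears only if it passes. If the group term is screened out, the reader gets no estimate and no interval for it, and may take its absence as evidence of no effect.

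**Working it through.** **1. The plan's own sample size.** The documents give 37 + 10 = 47 per group (Table 1, alpha 0.05, beta 0.10), and "the withdrawal rate is assumed to be 10" per cent. 47 × 1.10 = 51.7, so 52 per group, and 2 × 52 = 104. The Table 1 cell is reproduced by a Hanley-McNeil ROC calculation with AUC 0.80 against 0.50 and a 4:1 ratio of successes to non-successes: 37.2 + 9.3. The same inputs match the other cells to within about one child. The AUC values are not in the document; they were found by search.

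**2. Number of non-successes.** At the upper limit of the planning rate:
- 0.20 × 104 = 20.8 of all children
- 0.20 × 94 = 18.8 of those evaluable (2 × 47)
- 0.20 × 52 = 10.4 per group

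Ten candidates on 20 events is 20 / 10 = 2 events per candidate.

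**3. Chance of selecting at least one noise variable.** Assumptions: k independent noise candidates, entry at p<0.05. To a first approximation the chance is 1 − 0.95^k. The simulation is forward stepwise logistic regression with 104 children and 20 events.

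| Candidates k | 1 − 0.95^k | Simulated |
|---|---|---|
| 5 | 22.6% | 21% |
| 8 | 33.7% | 33% |
| 10 | 40.1% | 42% |
| 15 | 53.7% | 54% |

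Variations with k = 10:
- 94 children, 19 events: 41%
- 104 children, 10 events: 42%
- correlation of 0.3 between candidates: 35%
- backward elimination with removal at p>0.10: 65% (1 − 0.90^10 = 65.1%)

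Halving the events leaves the risk unchanged. It is driven by the number of candidates and the threshold. Where noise is selected with 20 events in 104, the mean apparent AUC of the model is 0.67 to 0.68 (8 to 10 candidates), against a true 0.50.

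**4. Chance of losing a real term.** Eight noise variables plus PI and group, 104 children, 20 events, forward selection.

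| True AUC of PI (group odds ratio 2) | PI dropped |
|---|---|
| 0.60 | 70% |
| 0.65 | 43% |
| 0.70 | 16% |
| 0.75 | 2.5% |
| 0.80 | 0.3% |

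| True odds ratio of group (PI AUC 0.70) | Group dropped |
|---|---|
| 1.5 | 88% |
| 2 | 78% |
| 3 | 48% |

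**5. What a fixed model can deliver.** PI ratio, group, interaction and age are four terms, so 20 / 4 = 5 events per term. In a simulated Firth model with 10 non-successes per arm, the 95% interval for the interaction spans a factor of about 3.1 to 3.8 either way. Power is about 16% if the AUC is 0.80 under one anaesthetic and 0.65 under the other, and only a little over half even for 0.80 v 0.50.

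**The case against.** The strongest reply is that candidates, thresholds and retained terms are details which a condensed article may leave to the full protocol or analysis plan. That stands for the candidate list, so about ten is an assumption here and the result is given as a range. It does not remove the point, because stepwise screening itself is written into the article.

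Several stronger readings are tempting and are not supported:

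- **Few events cause the noise selection.** They do not (step 3). They make selection unstable and cost real predictors.
- **There can be at most about 20 non-successes.** The 20% concerns ulnar nerve insufficiency in the literature. Block effect evaluation defines partial and failed block by HR, BP and RR rises during surgery and gives no rate, so the count could be lower or higher.
- **PI will be dropped.** At the AUC of 0.80 that reproduces Table 1, PI is lost from a pooled model in under 1% of runs. Separate models per anaesthetic would be more fragile, but the article does not plan them.
- **Recovery time, PACU stay and hospital stay will be used as predictors.** The article says only that they are recorded.
- **The trial's main analysis is compromised.** The regression is not called primary, and group comparisons have their own tests.

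It is also fair to say that a main effect of group on block success is not the question in Design of the study. The interaction is, and the text makes no provision for it.

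**Conclusion.** The point holds for the influencing-factor analysis of block effect. Followed as written, stepwise screening would select at least one noise variable in about 40% of trials with ten candidates. The range is 21% to 54% over 5 to 15 candidates, assuming forward entry at p<0.05, and backward elimination would do worse. The anaesthetic term would often be missing even with a true odds ratio of 2, given about 20 non-successes. Loss of PI is a material risk only if its AUC is about 0.70 or lower. The candidate count, the threshold and the use of the ulnar rate as a proxy for non-success are assumptions. This is a secondary analysis that should be corrected, and confidence is medium.

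**What to change.** Delete the stepwise screening for block effect. Replace it with one prespecified logistic model, for example Firth-penalised, of complete v not-complete block on PI ratio, anaesthetic group, PI ratio × group and age, with all four terms kept whatever their p-values. State that predictors must be measured before the block outcome is known, and that the intraoperative HR and BP changes which define the outcome may not serve as predictors. Report other factors, and complications, descriptively or label them exploratory.

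The cost is analysis wording only, with no further children or data. There are two downsides. Fewer influencing factors can be claimed. With about 20 events the interaction will have a wide confidence interval (step 5), so the text should say that it is read as an estimate and not as a decisive test of which anaesthetic suits PI better.
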